**Methods/design:**

We propose a double-blind, randomized controlled trial comparing methylprednisolone versus placebo in the treatment of CSDH without clinical and/or radiological signs of severity. The treatment will be administered daily for a duration of 3 weeks, at a dose of 1 mg/kg. The primary endpoint will be the delay of occurrence of surgical treatment at 1 month following the introduction of the treatment. Secondary endpoints will include the rate of recourse to surgery, survival rate, quality of life and functional assessments, occurrence of systemic secondary effects and radiological assessment of the response to treatment. This multimodal assessment will be done at 1, 3 and 6 months. Two hundred and two patients (101 per arm) are expected to be included considering our primary hypotheses.

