#### Secondary endpoints

Secondary evaluation criteria are: quality of life assessed by the Short Form 12-item (SF12) scale [28] at 1, 3 and 6 months; time to surgical treatment during the first 6 months (censored criteria); rate of surgical treatment of the CSDH at 1, 3 and 6 months; functional scales: daily living (Instrumental Activities of Daily Living; IADL) [29], cognitive (Mini-Mental State Examination; MMSE) [30] and the modified Rankin Scale [31] at 1, 3 and 6 months; plasma sodium, potassium and fasting glucose at days 0, 7, 14 and 21 and at 1 month; occurrence of adverse events potentially related to methylprednisolone (electrolyte disorders: hypokalemia, metabolic alkalosis, sodium retention (edema), hypertension, congestive heart failure; endocrine and metabolic disorders: Cushing’s syndrome, adrenal insufficiency, glucose disorders (impaired glucose tolerance, diabetes); gastrointestinal disorders: ulcer, perforation, gastrointestinal tract hemorrhage; skin disorders: acne vulgaris, purpura, hematoma, hypertrichosis; neuropsychological disorders: euphoria, insomnia, agitation, confusion, depression; ophthalmological disorders such as glaucoma); survival at 6 months; radiological improvement, defined by reduction of maximal thickness of hematoma and reduction of midline shift evaluated at 1, 3 and 6 months.

Subgroup analyses of all study endpoints will also be performed in subacute (less than 4 weeks old) and chronic (more than 4 weeks old) CSDH, and in patients treated or not treated with anticoagulant or platelet antiaggregant therapy.

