### Statistical analysis

Statistical analysis will be performed on all evaluated patients (intention-to-treat analysis in the methodology/biometrics unit of the Clinical Investigation Centre Inserm 1414 of Rennes. The statistical significance will be considered to be *p* values < 0.05 for all analysis.

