#### Analysis of other criteria

Student’s *t* test or a Mann-Whitney test if necessary will be used to compare quantitative variables. Quantitative criteria evaluated several times during the monitoring will be compared with repeated measures analysis of variance (ANOVA) with two factors (time, group). For qualitative criteria, a chi^2^ test will be used. For all these analyses, adjustments can be made in case of heterogeneity at inclusion.

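### The plan does not say whether the modified Rankin Scale is quantitative or qualitative, and neither route stated for a repeated or qualitative criterion is an ordinal analysis

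*Protocol article*

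**What the plan says.** Under Secondary endpoints, the Protocol article lists three functional scales together: IADL, MMSE and "the modified Rankin Scale [31] at 1, 3 and 6 months". It does not class any of them as quantitative or qualitative.

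Analysis of other criteria then sets the tests by type of variable:

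- Quantitative variables in general: Student's t test, or "a Mann-Whitney test if necessary will be used to compare quantitative variables".
- Quantitative criteria measured repeatedly: "Quantitative criteria evaluated several times during the monitoring will be compared with repeated measures analysis of variance (ANOVA) with two factors (time, group").
- Qualitative criteria: "For qualitative criteria, a chi^2^ test will be used". No trend or ordinal version is named.
- Adjustment is optional: "For all these analyses, adjustments can be made in case of heterogeneity at inclusion".

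The significance threshold under Statistical analysis is "values < 0.05 for all analysis". Baseline data collection already includes the mRS.

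**The concern.** The mRS is a set of ordered grades. It is measured three times, so the literal rules give two routes: ANOVA if it is quantitative, chi-square if it is qualitative. The ANOVA treats the steps between grades as equal. The Pearson chi-square treats the grades as unordered labels: its result is the same however the grades are permuted, so it cannot use the direction of a shift in disability. With 7 grades and two arms it spends (7 − 1) × (2 − 1) = 6 degrees of freedom.

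The Mann-Whitney test does use order. However, it is offered for quantitative variables if needed, and the next sentence sends repeated quantitative criteria to ANOVA.

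Function bears on whether a steroid is an acceptable alternative to surgery in the fragile population that the Discussion describes. The sample size was set for the surgery endpoint alone, so there is no planned margin of power for a functional scale.

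**Working it through.** **1. The plan's own figure.** The only sample-size statement concerns the primary endpoint: 80% v 60% operated on, 90% power, two-sided 0.05, 142 events, 202 patients.

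- Hazard ratio: ln(0.20)/ln(0.40) = 1.7565 (stated 1.756).
- Freedman events: [(HR + 1)/(HR − 1)]² × (1.960 + 1.282)² = (2.7565/0.7565)² × 10.51 ≈ 140.
- Patients: 140/0.70 = 200, where 0.70 is the mean of 0.80 and 0.60.

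Both results are within 2 of the stated values, and 202 × 0.70 = 141.4 rounds up to 142. The figure reproduces. It says nothing about power for the mRS.

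**2. Inputs for the mRS.**

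- From the article: 101 per arm, 1:1 allocation, alpha 0.05 (taken as two-sided).
- Not in the article, so assumed: 7 grades; proportional odds; common odds ratio (OR) from 1.25 to 4.0; four control-arm distributions from best to worst grade. These are mild (.25, .30, .20, .12, .08, .03, .02), fairly even (.10, .20, .20, .20, .15, .05, .10), uniform, and concentrated (.45, .30, .12, .06, .04, .01, .02).

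**3. Chi-square route.** Power at one visit from 20,000 simulated trials per scenario, 101 per arm, as a range over the four distributions. The loss is taken within each distribution.

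| Common OR | Chi-square, 7 grades | Mann-Whitney | Loss (points) |
|---|---|---|---|
| 1.25 | 7–8% | 14–15% | 6–7 |
| 1.5 | 15–18% | 33–37% | 18–20 |
| 1.75 | 27–33% | 55–62% | 28–29 |
| 2.0 | 42–50% | 72–80% | 29–30 |
| 2.25 | 57–67% | 85–90% | 23–28 |
| 2.5 | 69–79% | 91–96% | 17–22 |
| 3.0 | 85–93% | 98–99% | 7–13 |
| 4.0 | 97–99% | about 100% | 1–3 |

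For OR 1.5 to 2.5 the loss is therefore 17 to 30 points. With 85 per arm, to allow for missing data, it is 16 to 31 points.

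**4. Chi-square on collapsed grades.** For OR 1.5 to 2.5, against Mann-Whitney on the same levels, the loss is 14–22 points with 5 levels, 7–11 with 3 levels and none with 2. Dichotomising has its own cost against the full scale. In a further run (4,000 trials per scenario, three assumed distributions, OR 2.0), a cut at grade 2 or less had power 0.630, 0.501 and 0.698 against full-scale Mann-Whitney power of 0.790, 0.778 and 0.787. The losses are 16.0, 27.7 and 8.9 points.

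**5. Score route.** A t test on the grades at one visit stands in for the ANOVA group comparison. Against Mann-Whitney it loses about 0 to 5 points for three of the four distributions and up to about 10 for the concentrated one. For example, with 85 per arm, the concentrated distribution and OR 2.0: 0.653 − 0.553 = 0.100.

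Repeated-measures correlation was not modelled, so step 5 approximates the planned three-visit ANOVA.

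**The case against.** A reader might infer that the plan will analyse the mRS by chi-square and so give up 20 to 30 points of power. The article does not support this. It never assigns chi-square to the mRS. It lists the mRS beside IADL and MMSE at the same visits, and the natural reading sends all three to the repeated-measures ANOVA, where the loss is small. Pooling three visits might recover some or all of that loss. The large figure also needs all 7 grades, a mid-range effect and a distribution that the documents do not give.

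Two further objections have weight. First, an order-using test is already in the plan, and nothing bars a visit-by-visit Mann-Whitney comparison. Second, assigning methods endpoint by endpoint is often left to the full protocol or analysis plan, neither of which is shown and either of which may settle this. The article also does not single out the mRS: it is one of three functional scales among many secondary endpoints.

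These objections remove the claim of a large, certain loss. They do not remove the narrower point. The article does fix tests by class, leaves the class of this scale open, and offers no ordinal method on either literal route. The Mann-Whitney wording permits an ordinal comparison without prescribing one for the mRS, and optional adjustment does not turn the listed tests into an ordinal model.

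**Conclusion.** The point holds as a cheap improvement, not as an error that threatens the trial. The class of the mRS is unstated, and the size of the consequence depends on it:

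- Unordered chi-square on all 7 grades: about 17 to 30 points of power lost for OR 1.5 to 2.5 at 101 per arm, and less for smaller or larger effects. Against an order-using test on the same levels, the loss is also smaller when grades are collapsed.
- Grades as scores, as in the ANOVA: about 0 to 5 points, up to about 10 for a concentrated distribution.

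All these figures rest on assumed distributions, proportional odds and a single-visit comparison. The primary log-rank analysis and the 202-patient calculation are untouched.

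**What to change.** Add one sentence to Analysis of other criteria: the modified Rankin Scale at each of 1, 3 and 6 months will be analysed over its full ordered range with a proportional-odds model including treatment and baseline grade, reported as a common odds ratio, with patients who have died placed in the worst grade.

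The cost is that sentence. The baseline grade is already collected, so no new data are needed, and the sample size does not change. The small downside is reliance on proportional odds; a Mann-Whitney test at the same visit, already named in the plan, can be reported in support.

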#### Analysis of adverse events

Possible adverse events are coded according to the MedDRA classification and are the subject of a descriptive analysis.

### Data Safety Monitoring Board

An independent Data and Safety Monitoring Board is constituted before study initiation and comprises five members who are not involved in the study, including a neurosurgeon, a neurologist, an endocrinologist, a pharmacologist and a methodologist. The Data and Safety Monitoring Board meets after each interim analysis and at the end of the study. It can also meet on the request of the coordinating investigator or the methodologist if serious adverse events, or results which can jeopardize the existence of the protocol, occur. The Data and Safety Monitoring Board can propose to stop the study if interim statistical analyses reach significance or if it appears that study continuation would be contrary to ethics rules for safety reasons, or if the publication of trial results yields data that proves our hypothesis.

## Discussion

Although corticosteroids have previously been used in CSDHs, this practice has never been evaluated with a well-designed, high-quality-of-evidence study. Indications, duration and dosage and type of corticosteroid greatly vary depending on the habits of each team. In that context our study will help to clarify the prescription procedure.

Under physiological conditions the subdural space is a virtual space with histological continuity between the dura and the arachnoid. Various conditions, especially head injury, can lead to the separation of these two membranes. A proliferation of parietal cells can then occur in the subdural space, resulting in the formation of fibrous membranes in which capillaries proliferate under the influence of vascular endothelial growth factor [32]. These capillaries have inflammatory and permeable walls, and are partially responsible for the production of the subdural fluid [33]. This leakage contains partially degraded erythrocytes and coagulation factors, but the subdural liquid is uncoagulable because of the presence of large quantities of tissue plasminogen activator [34], a fibrinolytic enzyme. Inflammatory mediators, such as interleukin-6 and interleukin-8, platelet-activating factor and bradykinin [9] are also present in the subdural fluid, contributing to the persistence of inflammation.

With regard to these pathophysiological aspects of CSDH, corticosteroid use has been proposed to treat CSDH. The existing studies used varied methodologies, and had a low quality of evidence as demonstrated by a recent systematic review [35]. In a small study comparing patients treated with surgery (82 cases) and dexamethasone (26 cases), only one patient in the group with dexamethasone required secondary surgery [25]. In a retrospective series of 122 patients, only 20% of patients receiving dexamethasone prior to surgery required secondary surgery and the medical complications of treatment were essentially mild hyperglycemia [23]. In another retrospective study including 496 patients, preoperative corticosteroid administration seemed to reduce the recurrence rate of CSDH after burr-hole craniostomy without increasing the incidence of complications and treatment-related deaths [21]. A retrospective study testing the efficacy of corticosteroids as adjuvant therapy to surgery (142 patients with adjuvant corticosteroids and 56 patients without adjuvant corticosteroids) showed a trend toward a survival benefit with medical treatment (risk of death three-fold less in the case of adjuvant corticosteroids (*p* = 0.006)) [24]. Despite this data, there is a lack of published evidence concerning the efficacy of corticosteroids in reducing the rate of surgery. We have selected the 60% reduced rate of surgery based on our empirical experience with this treatment for this pathology.

Corticosteroids have the advantage of being well known and widely used for various pathologies. We arbitrarily chose to use methylprednisolone rather than dexamethasone because in France it is the most commonly used corticosteroid in neurosurgical pathologies. Even if diabetes is not a strict contraindication for the administration of corticosteroids, we added the presence of pre-existing diabetes as an exclusion criterion. We considered that the risk of including glycemic disorders with potentially severe consequences would exceed the benefit of avoiding surgery.

As mentioned above, one of the weaknesses of our work is the lack in the academic literature of studies describing the natural history of CSDH without treatment; some may claim that some cases of CSDH without clinical and neurological signs of severity could heal spontaneously. Another issue concerns the inclusion of patients with cognitive disorders. Confusion and dementia might be difficult to distinguish in an acute context, so the questioning of the relatives is of particular importance. We still wanted to include patients with doubtful or mixed semiology, who pose the greatest ethical dilemmas in everyday practice. A medical alternative to surgery in these cases would be of particular interest considering the invasiveness of surgery for that fragile population. However, corticosteroids might have psychic side effects liable to destabilize the mental status of such patients.

Another point of debate is the duration of corticosteroid therapy. After discussion with the endocrinology team of our establishment and on the basis of the academic literature [36–39], we decided to limit the treatment to 3 weeks. Indeed, after this period the risk of adrenocortical insufficiency induced after the discontinuation of corticosteroids increases significantly. Usually, adverse effects associated with corticosteroids predominantly occur during consumption of these medications over several weeks or months. We also decided to lower the inclusion boundary to a GCS score of 13. For those patients with a GCS score of 13 and, therefore, mild vigilance disorders, we recommend close monitoring in neurosurgical departments during the first days or the first week of treatment in order to assess the effectiveness of the treatment and possibly perform surgery in case of clinical deterioration. We left the choice to each of the investigators about the choice of timing to perform a secondary surgery.

Surgical drainage of CSDH finally remains the gold standard treatment. Even if the surgical procedure is simple, it can carry significant morbidity and mortality [7], especially in older patients with significant medical history. A medical alternative to surgery seems particularly relevant in these patients. Several surgical techniques are described in the academic literature. All these techniques aim at relieving the mass effect on the brain and try to minimize the risk of recurrence. The evacuation may be performed by craniotomy or by a single burr hole. Others propose a craniostomy allowing an evacuation of the hematoma in “closed skull” conditions [40]. The common goal of every technique is to wash maximally the subdural space while minimizing pneumocephalus. To perform this, the only technique that has been validated with a good level of evidence is the drainage of the subdural space, showing a recurrence rate decreasing from 24 to 9% with a subdural drain [41]. We left the choice of the surgical technique to each participating center, as well as the type of anesthesia and additional post-operative treatments (for example, the use of anticonvulsants). The perioperative management of anticoagulant and antiplatelet drugs is a particularly complex matter in the management of CDSH patients. Although these medications might be given for vital reasons, surgical treatment often requires their temporary suspension or decrease which could expose patients to cardiological or thromboembolic events. Our protocol leaves the choice to investigators to continue or discontinue these medications based on their team habits. The ideal management would be to treat patients with corticosteroids without stopping their antiplatelet or anticoagulant therapies. A specific study with high standard of proof would be useful to determine a clearer strategy on the management of these treatments in CDSH patients. In the meantime, subgroups analysis of this study might give some insights on that particular point.

## Trial status

This study protocol concerns an ongoing trial that has not completed patient recruitment at the time of submission.

## Abbreviations

IADL: Instrumental Activities of Daily Living
MMSE: Mini-Mental State Examination
